## 1.13 Comparator Vaccine

### 1.13.1 *Rationale for use of a comparator vaccine*

Having a comparator vaccine is particularly useful in phase 1 trials conducted in endemic areas, since background immunity and natural exposure to hookworm infection may otherwise make it difficult to interpret immunogenicity data. The use of a control group will permit comparison of immune responses between those vaccinated with *Na*-GST-1 and those not vaccinated with this antigen, and will result in a clearer interpretation of immunogenicity results. Although a placebo control group would accomplish the same goal, using a comparator vaccine that is beneficial to the participants increases the benefit-risk ratio, which is always relatively low in phase 1 trials.

Furthermore, the use of a comparator vaccine in a blinded study reduces potential investigator bias in reporting adverse events or attributing their causality. It will also safeguard against the probability that an excess of adverse events will be reported in this trial in comparison to an equivalent trial conducted in the United States. From prior experience conducting other trials at this study site, there will be many reported adverse events that are unrelated to the study

interventions: this rural population has reduced access to medical care and performs excessive heavy labour compared to an urban population or one living in the developed world. Thus, this population has significantly more medical afflictions than would be expected in a study population in the United States. Having a comparator arm in the study enables a fairer assessment of whether or not the rate of adverse events is “normal” or not, since to a reviewer unfamiliar with the study site, viewing the number of adverse events might otherwise lead to an erroneous – and negative – assessment of the vaccine’s safety.

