## 4.2 Sample Size and Estimated Duration of Study

A total of 102 participants will be enrolled (see **Section 10.2** for a justification of the sample size). Forty-eight will receive *Na*-GST-1/Alhydrogel® (one of three dose concentrations), 48 will *Na*-GST-1/Alhydrogel®/GLA-AF (one of three dose concentrations), and 6 will receive Butang® hepatitis B vaccine. The trial is expected to last for a total of 24 months. Each participant will be followed for 16 months from the time of the first injection.

In Part II of the study, in order to ensure that the vaccine formulations will be evaluated in individuals recently infected with hookworm, at least 4 individuals will be enrolled into each of Cohorts 7-12 who were infected with hookworm based on the fecal exam conducted during the

screening for the study, or who had a documented infection within 3 months of the date planned for the first vaccination for the participant.

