The investigators will be unblinded to participants' vaccine allocation status after all have had their study Day 140 visit (see **Section 8.10**). After this point, the study will be single-blinded (i.e., study participants will remain blinded to what vaccine they have received). The principal justification for unblinding the investigators before the final study visit has been completed is that the safety and immunogenicity data acquired during the vaccination phase of the study will be crucial in guiding the clinical development plan for *Na*-GST-1, and we feel that, to make an informed decision as to whether or not to proceed to pediatric trials, we must first assess the unblinded data in a timely fashion.

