6. Observe for at least 2 hours after vaccination to evaluate for immediate adverse reactions. During the 2-hour post-immunization wait period, study staff will discuss signs and symptoms of potential AEs.

Study Day 113 (1 day after Third Vaccination)

1. Perform basic history and physical exam (including injection site), emphasizing examination of any acute complaints.
2. Record vital signs.

Study Day 115 (3 +/- 1 days after Third Vaccination)

1. Perform basic history and physical exam (including injection site), emphasizing examination of any acute complaints.
2. Record vital signs.

Study Day 119 (7 +/- 1 days after Third Vaccination)

1. Perform basic history and physical exam (including injection site), emphasizing examination of any acute complaints.
2. Record vital signs.

Study Day 126 (14 +/- 2 days after Third Vaccination)

1. Perform basic history and physical exam (including injection site), emphasizing examination of any acute complaints.
2. Record vital signs.
3. Obtain blood for hematology, biochemistry, anti-GST-1 and total IgE antibody ELISAs, and cellular immunology assays.

Study Day 140 (28 +/-4 days after Third Vaccination)

1. Perform basic history and physical exam, emphasizing examination of any acute complaints.
2. Obtain blood for anti-GST-1 and total IgE antibody ELISAs and cellular immunology assays.
3. Obtain stool for examination for ova and parasites (Part II only).

Study Day 200 (3 months +/-14 days after Third Vaccination)

1. Perform basic history and physical exam, emphasizing examination of any acute complaints.
2. Obtain blood for anti-GST-1 and total IgE antibody ELISAs and cellular immunology assays.

Study Day 290 (6 months +/-14 days after Third Vaccination)

1. Perform basic history and physical exam, emphasizing examination of any acute complaints.
2. Obtain blood for anti-GST-1 and total IgE antibody ELISAs and cellular immunology assays.

Study Day 380 (9 months +/-21 days after Third Vaccination)

1. Perform basic history and physical exam, emphasizing examination of any acute complaints.
2. Obtain blood for anti-GST-1 and total IgE antibody ELISAs.
3. Obtain stool for examination for ova and parasites (Part II only).

Study Day 470 (12 months +/- 21 days after Third Vaccination)

1. Perform basic history and physical exam, emphasizing examination of any acute complaints.

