#### 8.1.3 Adverse Events of Special Interest (AESIs)

Special attention will be paid to monitoring for the occurrence of certain adverse events termed, "Adverse Events of Special Interest" or AESIs. These include inflammatory and autoimmune disorders that may potentially be related to the use of an immunostimulatory adjuvant (although none have been associated with the use of GLA-AF). The occurrence of the following AESI's will be closely monitored:

- Neuroinflammatory disorders (optic neuritis, multiple sclerosis, demyelinating disease, transverse myelitis, Guillain-Barre syndrome, myasthenia gravis, encephalitis, neuritis, Bell's palsy)
- Musculoskeletal disorders (systemic lupus erythematosus, cutaneous lupus, Sjogren's syndrome, scleroderma, dermatomyositis, polymyositis, rheumatoid arthritis, juvenile

rheumatoid arthritis, polymyalgia, rheumatica, reactive arthritis, psoriatic arthropathy, ankylosing spondylitis, spondylarthropathy)

- Gastrointestinal disorders (Crohn's disease, ulcerative colitis, celiac disease)
- Metabolic diseases (autoimmune thyroiditis, Grave's or Basedow's disease, Hashimoto thyroiditis, insulin-dependent diabetes mellitus, Addison's disease)
- Skin disorders (psoriasis, vitiligo, Raynaud's phenomenon, erythema nodosum, autoimmune bullous skin diseases)
- Others (autoimmune hemolytic anemia, idiopathic thrombocytopenic purpura, antiphospholipid syndrome, temporal arteritis, Behcet's syndrome, pernicious anemia, autoimmune hepatitis, primary biliary cirrhosis, primary sclerosing cholangitis, autoimmune glomerulonephritis, autoimmune uveitis, autoimmune cardiomyopathy, sarcoidosis, Stevens-Johnson syndrome).
- Vasculitides

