## **8.10 Breaking the Study Blind**

As outlined in **Section 4.4**, Part II of the study will be double-blinded until all study participants have completed their Day 140 visit, after which the investigators will be unblinded. During the double-blinded part of the study, a study participant's randomization code may be unblinded only for safety purposes. This is very unlikely to occur, as once a vaccine is administered, knowing which vaccine was given is unlikely to influence the medical management of an AE. This procedure is therefore exceptional and any decision to unblind will be discussed with the sponsor, the Principal Investigator, the Medical Monitor, and the SMC. If deemed necessary for urgent safety reasons, the Medical Monitor, in consultation with the SMC (if possible in a timely manner), may unblind a specific participant without revealing the study blind to the investigators or the Sponsor. Any unblinding will be thoroughly documented. It is to be emphasized that the Medical Monitor may put the study on hold at any time and discuss with the SMC. The decision to completely unblind or permanently stop the study prior to Day 140 will take the form of a formal recommendation by the SMC to the study Sponsor. The Principal Investigator must then notify the IRBs of this decision.

In the event that the investigators come to know the study code prior to final unblinding, the Principal Investigator must notify the Sponsor immediately. The reasons will be documented by the Principal Investigator and added to the study file.

Unblinding of the investigators will be done after all study participants have completed the Day 140 visit and upon authorization of the Sponsor. This will take place only after monitoring and verification of cGCP compliance by SVI, and after all safety and primary immunological results (i.e., antigen-specific IgG antibody levels as determined by ELISA) have been entered and the databases locked.

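### Part II investigators learn individual allocation after the Day 140 lock, while the primary adverse-event endpoint runs on to Day 470 with no cut-off or blinded assessor

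*Protocol*

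**What the plan says.** - **When the blind is lifted.** Section 4.4: "The investigators will be unblinded to participants' vaccine allocation status after all have had their study Day 140 visit". Section 8.10 agrees: "Unblinding of the investigators will be done after all study participants have completed the Day 140 visit and upon authorization of the Sponsor". It adds conditions: "This will take place only after monitoring and verification of cGCP compliance by SVI, and after all safety and primary immunological results" have been entered and the databases locked. The time this takes is not stated.
- **What remains blinded.** Section 4.4: "After this point, the study will be single-blinded (i.e., study participants will remain blinded to what vaccine they have received". No one other than participants is named as staying blinded.
- **Why.** Section 4.4 says the vaccination-phase results are needed promptly to decide on paediatric trials. Under Section 9.2.1 that decision rests on the second interim report.
- **How long follow-up lasts.** Section 4.2: "Each participant will be followed for 16 months from the time of the first injection". Clinical visits follow at Days 200, 290 and 380, and the last in Section 7.6 is "Study Day 470 (12 months +/- 21 days after Third Vaccination".
- **What is counted.** The primary objective (Section 2.1) is the frequency of related adverse events by severity, with no time limit. Section 8.1.1 counts events from every phase of the study. Section 8.2.2 has the investigator grade severity. Section 8.2.3 makes relatedness a five-level judgement, except that injection-site reactions are related by rule.
- **Why Part II is blinded.** Section 1.13.1: "the use of a comparator vaccine in a blinded study reduces potential investigator bias in reporting adverse events or attributing their causality".

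**The concern.** Relatedness and severity define the primary endpoint, and for systemic and unsolicited events both are matters of judgement. Section 1.13.1 expects many unrelated events at the Americaninhas site, so causality is the call that decides what enters the endpoint. Once the codes are released, those calls can be made by people who know who received GLA-AF, Alhydrogel alone or Butang. The special-interest list in Section 8.1.3 covers "inflammatory and autoimmune disorders that may potentially be related to the use of an immunostimulatory adjuvant", so knowing who received the adjuvant bears directly on those events.

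Before unblinding, the protocol keeps people who know the allocation, or might infer it, away from assessment: the vaccine manager (Section 7.3) and the vaccinators (Section 4.4). After unblinding no such separation exists, and no rule sets later events apart from the primary analysis. A difference between formulations in late related events would be open to assessment bias that could not be reliably removed afterwards.

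**Working it through.** **Inputs.** Part II has Cohorts 7, 9 and 11 with 10 participants each and Cohorts 8, 10 and 12 with 12 each (Section 4.1). First doses fall at weeks 0, 2, 2, 4, 4 and 5 for Cohorts 7 to 12; a footnote to Table 3 calls these intervals the minimum. The last visit is Day 470. The lag L from the last Day 140 visit to lock and code release is not given, so it is an assumption.

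**The protocol's own figures.** 3×10 + 3×12 = 66, as stated. Day 470 is 470/30.4375 = 15.4 months; the end of its window, Day 491, is 16.1 months. Both agree with 16 months after rounding.

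**Timing.** The trigger is the last participant's Day 140, so on the Part II calendar it falls at 5×7 + 140 + L = Day 175 + L. A cohort that started in week w is then on study day t = 175 + L − 7w. With L = 0:

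| Cohort | n | Start week | t | Days left (470 − t) | Share left | Person-days |
|---|---|---|---|---|---|---|
| 7 | 10 | 0 | 175 | 295 | 62.8% | 2,950 |
| 8 | 12 | 2 | 161 | 309 | 65.7% | 3,708 |
| 9 | 10 | 2 | 161 | 309 | 65.7% | 3,090 |
| 10 | 12 | 4 | 147 | 323 | 68.7% | 3,876 |
| 11 | 10 | 4 | 147 | 323 | 68.7% | 3,230 |
| 12 | 12 | 5 | 140 | 330 | 70.2% | 3,960 |

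The total is 20,814 of 66×470 = 31,020 person-days, or 67.1%.

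**Sensitivity.** Each day of lag removes 66 person-days, so the share is (20,814 − 66L)/31,020: 60.7% at L = 30, 54.3% at L = 60 and 47.9% at L = 90. Doubling the stagger with no lag gives 19,848/31,020 = 64.0%. So 67% is an upper figure.

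**Visits.** Section 7.6 schedules 22 clinical visits from Day 0 to Day 470, of which 4 (18%) come after Day 140. At nominal dates, a lag above 25 days keeps Cohort 7's Day 200 visit blinded, and a lag above 60 days does so for every cohort. At L = 90, Cohort 7 is at Day 265, so the Day 290, 380 and 470 visits are still unblinded for all 66 participants.

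**What is already protected.** All three doses and the checks 1, 3, 7, 14 and 28 days after each come before unblinding. The last scheduled haematology and biochemistry are at Day 126 (Section 7.6, Appendix B).

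**What the blind hides beforehand.** Cohort membership is known. Guessing the majority arm from cohort alone is right for 3×8 + 3×10 = 54 of 66 participants (82%).

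**Leverage of one call.** If one reattributed event changes a participant's status, the proportion moves by 1/10 = 10 percentage points in a Part II GLA-AF dose group and by 1/6 = about 17 points in the Butang group (6 recipients, Section 4.2).

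**The case against.** The strongest reply is that this is a disclosed and justified choice with safeguards. Vaccination-phase data are monitored and locked before any code is released, so late unblinding cannot touch them. Only a minority of visits remain, injection-site reactions cannot be reattributed, and no scheduled safety laboratory grading is exposed. The blind is also partial: Part I is open-label, dose is known in Part II, and cohort alone gives the right arm for 82% of participants. The trial is not powered for group comparisons (Section 10.2).

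Most of this stands and limits the size of the point. Disclosure does not answer it. The paediatric decision needs results by arm; nothing in the protocol shows why clinicians who assess events need participant-level codes. Few visits does not mean few events either, since in Part II participants can report to a study clinician at any time (Section 8.2.1). And an informed guess from cohort is weaker than certain knowledge, especially for the minority arms: Butang in Cohorts 7, 9 and 11, and Alhydrogel alone in Cohorts 8, 10 and 12.

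Stronger readings are tempting but not supported:

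- That each participant is unblinded at his or her own Day 140. The trigger is the last participant's visit plus lock.
- That two thirds of the adverse-event data are unblinded. The 67% is calendar time, at its upper limit.
- That a special-interest risk window falls after unblinding, or that such events are expected late. Section 8.1.3 gives no start, end or risk period.
- That blinding was meant to eliminate investigator bias. Section 1.13.1 claims only to reduce it.

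**Conclusion.** The point holds in a limited form. For Part II, the protocol lets investigators know individual allocation while they continue to assess events that count towards a primary endpoint with no end date, contrary to its own reason for blinding. It names no blinded assessor and no separate reporting for that period.

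Exposure is at most about 67% of Part II person-time, assuming minimum stagger and no lag to lock, and about 48% to 61% for assumed lags of 90 to 30 days. It covers at most 4 of 22 scheduled clinical visits. The data at risk are severity and causality calls on late systemic and unsolicited events, including any of special interest. Vaccination-phase reactogenicity and scheduled safety laboratory results are not affected. The direction and size of any bias cannot be calculated from the protocol. The change is worth making because it is cheap and groups are small enough for a single call to matter.

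**What to change.** **Sections 4.4 and 8.10.** After lock, release participant-level codes only to the sponsor, the reporting statistician and the Safety Monitoring Committee (which already has access under Section 8.4.2). Give investigators group-level results in the second interim report. Keep every clinician who grades or attributes adverse events blinded to individual codes until the last Day 470 visit. The existing route for unblinding on safety grounds need not change.

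**Section 10.1.1.** Base the between-formulation comparison of related adverse events in Part II on the blinded, locked data. Report events arising after unblinding separately, labelled as unblinded assessments. This second change is the minimum if the firewall cannot be kept.

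**Cost.** Mainly protocol wording and control of who sees the codes; no added visits and no delay to the paediatric decision. Investigators would see participant-level listings by arm later than now planned. With groups this small, group tables may still reveal some individuals, particularly for a rare event, so the firewall reduces the problem without removing it.

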## **5 SELECTION OF PARTICIPANTS**

### **5.1 Inclusion Criteria**

1. Males or females between 18 and 45 years, inclusive.
2. Good general health as determined by means of the screening procedure.
3. Available for the duration of the trial (16 months).
4. Willingness to participate in the study as evidenced by signing the informed consent document.
5. For Part II only: Negative for hookworm during screening, or if found to be infected with hookworm, has completed a course of three doses of albendazole.

### **5.2 Exclusion Criteria**

1. Pregnancy as determined by a positive urine hCG (if female).
2. Participant unwilling to use reliable contraception methods up until one month following the third immunization (if female and not surgically sterile, abstinent or at least 2 years post-menopausal).
3. Currently lactating and breast-feeding (if female).
4. Inability to correctly answer all questions on the informed consent comprehension questionnaire.
5. Evidence of clinically significant neurologic, cardiac, pulmonary, hepatic, rheumatologic, autoimmune, diabetes, or renal disease by history, physical examination, and/or laboratory studies.
6. Known or suspected immunodeficiency.
7. Laboratory evidence of liver disease (alanine aminotransferase [ALT] greater than 1.25-times the upper reference limit).
8. Laboratory evidence of renal disease (serum creatinine greater than 1.25-times the upper reference limit, or more than trace protein or blood on urine dipstick testing).
9. Laboratory evidence of hematologic disease (absolute leukocyte count  $<3200/\text{mm}^3$  or  $<3500/\text{mm}^3$  [in Americaninhas and Belo Horizonte, respectively]; absolute leukocyte count  $>10.8 \times 10^3/\text{mm}^3$ ; hemoglobin  $<11.4 \text{ g/dl}$  or  $<12.0 \text{ g/dl}$  [females in Americaninhas and Belo Horizonte, respectively] or  $<12.1 \text{ g/dl}$  or  $<13.5$  [males in Americaninhas and Belo Horizonte, respectively]; absolute lymphocyte count  $<900/\text{mm}^3$ ; or, platelet count  $<130,000/\text{mm}^3$  or  $<140,000/\text{mm}^3$  [in Americaninhas and Belo Horizonte, respectively]).
10. Laboratory evidence of a coagulopathy (PTT or PT INR greater than 1.1-times the upper reference limit [in Belo Horizonte] or PT INR greater than 1.3 [Americaninhas]).
11. Serum glucose (random) greater than 1.2-times the upper reference limit.
12. Other condition that in the opinion of the investigator would jeopardize the safety or rights of a volunteer participating in the trial or would render the subject unable to comply with the protocol.
13. Participation in another investigational vaccine or drug trial within 30 days of starting this study.
14. Volunteer has had medical, occupational, or family problems as a result of alcohol or illicit drug use during the past 12 months.
15. History of a severe allergic reaction or anaphylaxis.
16. Severe asthma as defined by the need for regular use of inhalers or emergency clinic visit or hospitalization within the last 6 months.

17. Positive ELISA for HCV.
18. Positive ELISA for HBsAg.
19. Positive ELISA for HIV.
20. Use of corticosteroids (excluding topical or nasal) or immunosuppressive drugs within 30 days of starting this study.
21. Receipt of a live vaccine within past 4 weeks or a killed vaccine within past 2 weeks prior to entry into the study.
22. History of a surgical splenectomy.
23. Receipt of blood products within the past 6 months.
24. History of allergy to yeast.
25. Anti-*Na*-GST-1 IgE antibody level above 0.35 kUA/L by the ImmunoCAP method.
26. For Part I only: history of previous infection with hookworm; residence for more than 6 months in a hookworm-endemic area; or, positive for hookworm infection on screening microscopic fecal examination.
27. For Part II Cohorts #7, #9, and #11 only: previous receipt of a primary series of any hepatitis B vaccine.

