## **7.7 Laboratory Testing**

Using standard techniques, the following tests will be performed at the Humberto Abrão clinical laboratory in Belo Horizonte, Minas Gerais, Brazil, in Part I of the study or the Carlos Chagas clinical laboratory in Governador Valadares, Minas Gerais, Brazil, for Part II of the study.

1. Complete blood count plus white blood cell (WBC) differential\*
2. Serum creatinine
3. Alanine aminotransferase (ALT)
4. Serum glucose (random)
5. HBsAg ELISA

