6. HCV ELISA
7. HIV ELISA
8. Prothrombin time - International Normalized Ratio (PT INR) [Part I only]
9. Partial thromboplastin time (PTT) [Part I only]

Urine hCG testing will be performed at the clinical trial sites using urine pregnancy test kits that have been approved by Brazilian and/or US regulatory agencies. Urine dipstick testing will also be performed at the trial sites using an approved product.

For Part II of the study, PT INR testing will be performed at the study site in Americaninhas using an FDA-approved portable, point-of-care instrument. Due to the distance between the field site and the Carlos Chagas clinical laboratory (approximately 4-5 hours' drive), it will not be possible to send blood collected from volunteers to this laboratory for PTT and PT/INR testing within the acceptable time limit.

Anti-*Na*-GST-1 ELISAs will be performed at FIOCRUZ in Belo Horizonte, Brazil, as will the exploratory immunology assays.

\*The following CBC parameters will be assessed for safety throughout the trial: WBC, absolute neutrophil count, hemoglobin concentration and platelet count.

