### **8.5 Criteria for Suspension of Further Injections**

If a dose of vaccine is considered significantly reactogenic (see below), dose escalation and/or additional vaccinations will be suspended until reviewed by the Medical Monitor, SMC and study sponsor (SVI). Any recommendation of the Medical Monitor and SMC to resume or suspend further injections (either for an individual participant, an entire dose cohort, or all dose cohorts) will be communicated in writing to the sponsor and Principal Investigator. All communications from the SMC will subsequently be forwarded by the investigators to the CPqRR and GWUMC IRBs.

The following criteria will be used to define significant reactogenicity (note that in Part II of the study, these apply to both the *Na*-GST-1 vaccines and Butang® vaccine, as these criteria will be applied in advance of any consideration of unblinding):

- a. One or more participants experience an SAE (as defined in **Section 8.1.2** in this protocol) that is determined to be possibly, probably, or definitely related to the vaccine (as defined in **Section 8.2.3** in this protocol), **OR**
- b. One or more participants experience a hypersensitivity reaction (a Grade 3 allergic reaction, as defined in **Appendix D**) that is possibly, probably or definitely related to the vaccine, **OR**
- c. One or more participants in a single dose cohort experience an objective physical finding or laboratory abnormality of Grade 3 or higher (with the exception of isolated Grade 3 erythema or swelling), as defined in **Section 8.2.2** in this protocol, that is determined to be probably or definitely related to the vaccine. **OR**

- d. Two or more participants in a single dose cohort experience a Grade 2 or higher safety laboratory abnormality or Grade 3 clinical AE that is possibly, probably or definitely related to the vaccine.

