| Stool examination                     |              |     | X                |          |   |   |   |     |     |          |    |    |    |     |     |          |     |     |     |     | X  |     |     | X  |     |
| Blood Volume (mL)              |              |     | 30               | 50       |   |   |   | 50  | 40  | 50       |    |    |    | 50  | 40  | 50       |     |     |     | 50  | 40             | 40  | 40  | 10             |     |
| Total Blood Volume (mL)        |              |     | 30               | 80       |   |   |   | 130 | 170 | 220      |    |    |    | 270 | 310 | 360      |     |     |     | 410 | 450            | 490 | 530 | 540            | 540 |

CBC parameters to be assessed for safety: WBC, absolute neutrophil count, hemoglobin, and platelet count

To be completed within 90 days of enrolment.

Part II of the study only.

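### Exclusion 9 sets no entry limit for the neutrophil count, a graded CBC safety parameter, so a volunteer already in a Grade 2-3 band is kept out only by investigator discretion

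*Protocol*

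**What the plan says.** **Entry.** Exclusion 9 in section 5.2 begins "Laboratory evidence of hematologic disease (absolute leukocyte count" and sets limits for total leukocytes (low and high), hemoglobin by sex, lymphocytes and platelets. Most of them differ between Belo Horizonte and Americaninhas. None of the 27 exclusion criteria or the five inclusion criteria gives a neutrophil value.

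**Monitoring.** Section 7.7 states: "The following CBC parameters will be assessed for safety throughout the trial: WBC, absolute neutrophil count, hemoglobin concentration and platelet count". The footnote to Appendix B repeats the list: "CBC parameters to be assessed for safety: WBC, absolute neutrophil count, hemoglobin, and platelet count".

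**Grading.** Appendix C grades a fall in ANC on its absolute value at both sites. Only hemoglobin has a second row for change from Day 0.

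**Consequences.** Criterion 8.5(c) opens "One or more participants in a single dose cohort experience an objective physical finding or laboratory abnormality of Grade 3 or higher" and requires probable or definite relatedness. Criterion 8.5(d) opens "Two or more participants in a single dose cohort experience a Grade 2 or higher safety laboratory abnormality" and requires at least possible relatedness. Under section 4.1 the trial does not move to Part II, or to the next dose in Part II, if a section 8.5 criterion is met.

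**Availability of the value.** The first test listed in section 7.7 is "Complete blood count plus white blood cell (WBC) differential", and Appendix B schedules a CBC at screening and on Day 0.

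**The concern.** Entry limits and grading tables work together. If entrants start at Grade 0 on a parameter, a later grade means that something changed during the trial. Exclusion 9 achieves this for the other graded CBC parameters, apart from values exactly on a limit, but not for neutrophils.

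Someone who enters with a low ANC carries a graded value from the start, and no Day 0 comparison is built into the ANC grade. A small fluctuation can then cross a grade boundary. Whether that is a vaccine effect or baseline variation becomes a judgement made case by case. The judgement feeds the primary objective (vaccine-related AEs by severity) and the section 8.5 criteria. It can go wrong in either direction: variation may be counted as a signal, or a real effect dismissed as baseline. This is the first use of the antigen in humans, in cohorts of 6 to 12.

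**Working it through.** **1. Entry limits against the Appendix C Grade 1 edge**

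| Parameter | Part I: excluded if / Grade 1 edge | Part II: excluded if / Grade 1 edge |
|---|---|---|
| WBC, low (/mm³) | <3500 / 3500 | <3200 / 3200 |
| WBC, high (/mm³) | >10,800 / 10,800 | >10,800 / 10,800 |
| Hemoglobin, males (g/dL) | <13.5 / 13.4 | <12.1 / 12.0 |
| Hemoglobin, females (g/dL) | <12.0 / 11.9 | <11.4 / 11.3 |
| Platelets (/mm³) | <140,000 / 140,000 | <130,000 / 130,000 |
| ANC (/mm³) | no limit / 1599 | no limit / 1000 |

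The two chemistry tests in Appendix C also have entry limits: ALT in exclusion 7 and creatinine in exclusion 8. ANC is the only laboratory test in Appendix C without one.

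**2. Do the other limits keep a low ANC out indirectly?**

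ANC = WBC − lymphocytes − other white cells.

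- Part I: 3600 − 2500 − 400 = 700, which is Grade 3 (500-749).
- Part II: 3300 − 2400 − 500 = 400, which is Grade 3 (300-499).

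Both meet the leukocyte floor (3500 and 3200) and the lymphocyte floor (900).

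More generally, take WBC at its floor and subtract the ANC and the 900 lymphocyte minimum. If the remainder is not negative, the combination passes:

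- Part I, Grade 2 (750-999): 3500 − 999 − 900 = 1601, up to 3500 − 750 − 900 = 1850.
- Part I, Grade 3 (500-749): 1851 to 2100.
- Part II, Grade 2 (500-749): 3200 − 749 − 900 = 1551, up to 3200 − 500 − 900 = 1800.
- Part II, Grade 3 (300-499): 1801 to 2000.

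All are positive, so the leukocyte and lymphocyte limits do not act as a neutrophil limit.

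**3. How small a fall changes the grade?**

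- Part I, entering at Grade 1: 1000 to 990 moves to Grade 2 (10/1000 = 1.0%).
- Part I, entering at Grade 2: 760 to 740 moves to Grade 3 (20/760 = 2.6%).
- Part II, entering at Grade 2: 510 to 490 moves to Grade 3 (20/510 = 3.9%).

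**4. How often?**

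The protocol gives no neutrophil distribution for either population. Assume that a proportion p of entrants, independently, start in a low band, with p from 1% to 5%. The chance of at least one in a cohort of n is 1 − (1−p)^n. The chance of two or more is 1 − (1−p)^n − np(1−p)^(n−1).

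| n | p = 1%: one or more / two or more | p = 5%: one or more / two or more |
|---|---|---|
| 6 | 5.9% / 0.1% | 26.5% / 3.3% |
| 10 | 9.6% / 0.4% | 40.1% / 8.6% |
| 12 | 11.4% / 0.6% | 46.0% / 11.8% |

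These are chances of low starting values in one cohort. They are not chances of an AE or of a suspension, each of which needs further steps.

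**The case against.** The strongest reply is that exclusion 9 is not the only gate. Inclusion 2 requires satisfactory general health on screening, exclusion 6 covers suspected immune deficiency, and exclusion 12 lets the investigator turn away anyone thought to be at risk. The worked examples need lymphocytes at 2500/3600 = 69% and 2400/3300 = 73% of white cells, which a clinician with the differential would probably notice. This stands. A reader might infer that a person with Grade 3 neutropenia is simply eligible, but the protocol supports only the narrower statement that no numeric criterion excludes them.

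The second reply concerns the consequences. Section 8.1.1 defines an AE as a change, including worsening of an existing condition, so a stable low value is not an AE. Hematology is drawn before the first injection, so the baseline is on record. The primary objective and criteria 8.5(c) and (d) all depend on a relatedness judgement, and section 8.5 imposes a hold pending review. This stands too. A reader might infer that dosing would be suspended because of a pre-existing value, but the documents do not support that. What survives is that a small fall from a low start can count as a change, and the ANC grade does not show how small it was.

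A reader might also infer that screening lymphocytes is itself a mistake because Appendix C does not grade them. It is not. Random glucose and coagulation are likewise screened without an Appendix C row, and section 8.2.2 refers other clinically significant laboratory abnormalities to Appendix D.

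Finally, no rule in the protocol requires every graded parameter to have an entry limit, so no statement is contradicted. That is correct. The case rests on the protocol's own consistent practice for every other laboratory test in Appendix C.

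**Conclusion.** The point holds as a gap in alignment between exclusion 9 and the safety grading. ANC is a named safety parameter, is graded on absolute value, can count toward 8.5(c) and (d), and is the only Appendix C laboratory test with no numeric entry limit. The other blood-count limits leave room for Grade 2 and Grade 3 values at both sites. Protection therefore depends on discretion applied without a stated threshold.

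The effect is on interpretation: an avoidable baseline confounder in the primary safety data and in the suspension criteria. Its frequency cannot be derived from the protocol. On an assumed 1% to 5% of low entrants, one such person in a given cohort is plausible (5.9% to 46.0%). Two or more is uncommon (0.1% to 11.8%), before any requirement for a further fall or a relatedness judgement. The finding does not depend on these figures. It is a modest weakness with a cheap remedy.

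**What to change.** Reconcile exclusion 9 with section 7.7 and Appendix C so that ANC, like the other graded CBC parameters, has an entry limit for each site consistent with the Appendix C grading. The sponsor should set the values. For orientation only, Appendix C starts Grade 1 at 1599/mm³ in Part I and 1000/mm³ in Part II.

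The value can be read from the differential already obtained at screening, so no new test, visit or blood volume is needed. The cost is one line in exclusion 9 and a few extra screen failures.
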